**Binge drinking**

Questions in CONOR:

“Approximately how often during the past 12 months have you consumed alcohol corresponding to at least 5 glasses of liquor in 24 hours?”

In all 47,848 participants (26,151 men and 21,697 women), and answers varied from zero to 99 times during the last year. Nearly half (46.3%) reported zero, and the frequency was a higher in men than in women.

In NTR:

1990 questionnaire: “Approximately how many times during one year do you drink more than 5 bottles of beer, one bottle of red or white wine or a quarter bottle of liquor?” (Never, 1-4 times a year, 5-10 times a year, once a month, 2-3 times a month, once a week, 2-4 times a week or every day or almost every day?)

Life course socioeconomic position: Highest educational level, household income (yearly updated), Childhood parental occupational class and education, and housing conditions from Censuses 1960 onwards).

Cognitive ability/Intelligence in late adolescence: The Norwegian National Conscript Service examines more than 90% of the male population at age 18-19 years. General ability is a composite score based on 3 speeded subtests. The Arithmetic Test (25 minutes) has 30 items in prose and measures logical reasoning and arithmetic and algebraic ability; it is similar to the arithmetic test in the Wechsler Adult Intelligence Scale (WAIS). The Word Similarities Test (8 minutes) is a multiple-choice test with 54 items, akin to the vocabulary test in WAIS. The Figures Test (20 minutes) has 36 multiple-choice items with 6 or 8 alternatives and is similar to Raven’s Progressive Matrices.

The CONOR mental health index: This consists of summative index including seven questions on mental distress scored 1-4: “Have you, in the course of the last two weeks, felt: Nervous and unsettled? Troubled by anxiety? Secure and calm? Irritable? Happy and optimistic? Sad/depressed? Lonely?” Response categories are “No”, “A little”, “Quite a bit” and “Very”. This index captures a combination of symptoms of anxiety and depression. This index has been validated, has good internal consistency and correlates highly with the total score for Hospital Anxiety and Depression Scale (HADS) ( $r=0.76$ ) and with Hopkins symptom checklist (HSCL-10) ( $r=0.70$ ).

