## **Statistical methods**

Sample size and power: The materials used to address RQ 1 is considerably higher powered than those used in previous research. Power calculations have been conducted using the `sampsi` command in STATA and the program `Quanto` for interaction terms. RQ 1: Two options have been used: Either to report the effect of moderate alcohol consumption adjusted for binge drinking or to test formally for interaction between average alcohol consumption and reported binge drinking. We have calculated the last because we consider this the most conservative approach. The relative risk of main effects has for average alcohol consumption reported to be 0.75 and for binge drinking 1.45. If we assume that 10 % in the cohort develop CVD in the follow up period, power of 80 % and set p-value at 5 % for two sided tests, we would need a sample of 7,960 individuals, which is well below our sample of 55,876 individuals. RQ 2 and 3: Prevalence of mental distress in CONOR is on average 10 %, and the effect of depression on CVD is assumed to be 1.6. If we want to detect a 50 % difference in effect of binge between depressed and not depressed subjects, we would need 26,740 individuals (in our sample  $n=47,848$ ), and for frequency of alcohol use 53,680 individuals (in our sample  $n=162,048$ ). RQ 4: As we do not know the strength of association between alcohol consumption and sibling and parental CVD morbidity and mortality, it is difficult to calculate sample size exactly for this sub study. For this reason, we have preliminary investigated this issue, and found that it appears to be higher risk of CVD in fathers and same sexed sibling among those who are abstainers compared to those who drink moderately. The hazard ratio of CVD death in fathers among those who abstain from alcohol compared to moderate drinkers was 0.93 (0.88-0.99). RQ 5: It is not straightforward to estimate power in within sibling analyses. With a total of 5050 CVD endpoints, and based on our experiences in an analysis with similar design and number of endpoints, we consider it likely that we will be able to detect differences large enough to be theoretically interesting. RQ 6: With 3500 alcohol related cases, we consider it highly likely that we will be able to detect meaningful degree of familial aggregation for mental distress and CVD morbidity and mortality.

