Data analysis: For time to event outcomes such as morbidity and mortality the primary modelling strategy is to use Cox proportion hazard regression models. In RQ 1 the effect of moderate alcohol consumption will be analysed by adjusting for binge drinking and across strata of binge drinking (interaction term will be fitted to formally test if the effect differs). In RQ 2-3 the same strategy will be employed using strata of cognitive ability and mental health. In RQ 4 the aim is to see if using alcohol consumption among family members as instrumental variable will reproduce a protective effect of moderate alcohol consumption as seen in conventional analysis. Using instruments, it will also be possible to estimate the effect sizes and compare the effect and pattern in CONOR participants with that of their sibling. To achieve this, z-scores will be calculated based on units of alcohol consumption reported. For RQ 5, the effects of alcohol consumption will be estimated by comparison between siblings or co-twins ("fixed effect"). This approach effectively matches out all factors shared between siblings that may confound the effect of alcohol on cardiovascular mortality reported in studies of unrelated individuals. The analyses will be conducted in the statistical software STATA. Age, smoking status and number of cigarettes per day in smokers, physical activity, self-reported disease (CVD, diabetes, antihypertensive medication) and psychosocial distress at baseline will be adjusted for as potential confounders. In

familial aggregation analysis, we will estimate to what extent alcohol related mortality co-occur in first degree family members with CVD morbidity and mortality and mental distress by summing up number of family members with any of these traits.

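### RQ 2-3 are to be analysed on strata of mental distress and cognitive ability although scores are held for both; if modification is graded, the interaction test loses information and coarse strata adjust incompletely

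*Protocol*

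**What the plan says.** The research questions ask, for mental distress (RQ 2) and for cognitive ability and socioeconomic factors (RQ 3), whether each accounts for the alcohol effect and whether it modifies that effect.

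The data-analysis paragraph under Statistical methods sets the method: "In RQ 2-3 the same strategy will be employed using strata of cognitive ability and mental health". The strategy referred to is that of RQ 1: "adjusting for binge drinking and across strata of binge drinking (interaction term will be fitted to formally test if the effect differs". It therefore has two parts, adjustment for the factor and an analysis by strata with an interaction term. Neither the number of strata nor the cut-points are given.

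The variable descriptions (Main variables) present both factors as scores. Of the CONOR mental health index: "This consists of summative index including seven questions on mental distress scored 1-4". Of cognitive ability: "General ability is a composite score based on 3 speeded subtests".

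The power paragraph treats distress as a yes/no factor: "Prevalence of mental distress in CONOR is on average 10 %, and the effect of depression on CVD is assumed to be 1.6". It asks for a 50% difference in the binge effect between the two groups and arrives at 26,740 people (47,848 available), or 53,680 for drinking frequency (162,048 available). It gives no power figure for cognitive ability.

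The covariate list ends with "psychosocial distress at baseline will be adjusted for as potential confounders", form unstated. Cognitive ability is not in that list. Data sources and Samples also name the Social Security Registry for mental health problems; that source is a diagnosis, not a score.

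**The concern.** Cutting a score into groups discards the differences within each group. This matters in two ways here.

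- **Interaction test.** If the alcohol effect shifts gradually with distress or ability, a product term on the score uses all of that gradient. A term on strata uses only the differences between group means.
- **Adjustment.** If the strata also serve as the adjuster, confounding within strata remains. An alcohol association that the factor really does account for would then look partly unexplained, and the answer would lean towards independence. Distress at least appears as a covariate. For cognitive ability the stratified strategy is the only handling the Protocol states, and the score comes from male conscripts only.

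**Working it through.** **1. The plan's own figure.** The Protocol gives no exposure prevalence for the RQ 2-3 calculation, so 26,740 cannot be confirmed. A Wald test of the product term of two binary factors (logistic, ratio 1.5, population risk 10%, distress 10%, binge effect 1.45) gives 26,740 at a binge prevalence of about 14%. It gives about 17,900 at 53.7%, the share reporting any binge episode (100 - 46.3). The figure is attainable. The 10% risk, 80% power and 5% two-sided level are stated for RQ 1 and assumed to carry over.

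**2. Power of the two-group test on the plan's N.** Power = Φ(2.80 × √(n/N) - 1.96).
- Binge: n/N = 47,848/26,740 = 1.79, power 96%.
- Frequency: 162,048/53,680 = 3.02, power over 99%.

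**3. Information kept by strata if modification is linear in the score.** This is the squared correlation between the score and its grouped version. For a split with upper share q of a normal score it is φ(c)²/[q(1 - q)].

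| Grouping | Kept | Lost |
|---|---|---|
| 10/90, normal: (0.1755/0.3)² | 34% | 66% |
| 10/90, exponential: (0.1 × ln 10/0.3)² | 59% | 41% |
| Median split, normal: 2/π | 64% | 36% |
| Tertiles, normal | 79% | 21% |
| Quintiles, normal | 90% | 10% |

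For the same graded effect, 26,740 with a 10/90 split corresponds to about 26,740 × 0.342 = 9,150 with the full score (normal), or 26,740 × 0.589 = 15,750 (exponential). A logistic simulation at n = 26,740 agrees: 79% power for the split, against 97% (normal) or 93% (skewed) for the score.

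**4. Binge sample at a lower CVD risk.** Samples gives 547 CVD deaths among the 47,848. The Approaches section puts cases at three to four per death: 1,641 to 2,188 cases, a risk of 3.4-4.6%. A simulation at those risks (binge 1.45, distress 1.6, interaction 1.5, 53.7% binge, 300 runs) gave:

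| Score | Risk | 10/90 split | Full score | Gain |
|---|---|---|---|---|
| Normal | 3.4% | 80% | 98% | 18 |
| Normal | 4.6% | 89% | 99% | 10 |
| Skewed | 3.4% | 90% | 99.7% | about 10 |
| Skewed | 4.6% | 97% | 99.7% | about 3 |

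At 10% risk both tests exceed 96%.

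**5. When the score does worse.** If the true modification is a step exactly at the top 10%, the linear term falls to 44% power (normal) or 61% (skewed), against 79% for the split, at n = 26,740.

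**6. Adjustment.** A 10% indicator leaves 1 - 0.342 = 66% of a normal score's variance uncontrolled. With an assumed score-exposure log odds ratio of 0.2 to 0.4 per SD and a true binge odds ratio of 1.45, adjusting for the indicator gives about 1.47 to 1.53. Adjusting for the score gives about 1.43 to 1.46.

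**The case against.** The case on the other side is substantial, and much of it stands.

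- **A 10/90 cut is not the stated analysis.** A reader might infer from the power paragraph that RQ 2-3 will use a 10% yes/no group. The data-analysis paragraph says only strata; with quintiles the loss is about 10%. Cut-points may properly sit in a SAP that is not shown, so leaving them open is no finding. What can be criticised is the stated choice of strata where scores exist.
- **Under-adjustment is a risk, not a fact.** The strategy includes adjustment for the factor, and distress is a listed covariate. Nothing says that adjustment uses a coarse indicator.
- **Not every measure is a score.** The registry source is a diagnosis, and a comparison of distressed with non-distressed people is a group contrast that strata answer directly.
- **The plan meets its own target.** On its assumptions the two-group test has 96% power in the binge sample and more in the larger one.
- **A larger gain is tempting but unsupported.** Scaling 26,740 inversely with risk gives 58,476 to 77,968, hence 72% to 59% power for a 10/90 split. Against 91% (skewed) and 96% (normal) for the score, a reader might infer gains of 19-37 points. Direct simulation at the same risks gives 3-18, because the plan's N implies a lower binge prevalence than the sample shows. The risk is also uncertain: 9,735 infarctions plus 8,926 strokes per 3,774 CVD deaths is 4.9 cases per death, a risk of about 5.7% and 80% power on the same scaling.
- **No power figure can be derived for cognitive ability.** Setting the at most 26,151 men in the binge sample against 26,740 misuses an N computed for a 10% factor; the Protocol states no effect size for ability.
- **A linear term can lose.** The threshold result above is not trivial, so strata cannot simply be dropped.

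**Conclusion.** The point holds as an efficiency and adjustment concern. It is not evidence that RQ 2-3 are underpowered for the plan's target. Where the CONOR index or general ability is used, strata lose 10% (quintiles), 21% (tertiles) or 36% (median split) of the information for a graded interaction, and 41-66% if the two-group contrast of the power paragraph were carried into the analysis.

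The gain in power depends on the strata chosen, the shape of the effect and the CVD risk. It is small at 10% risk and in the 162,048 sample, and about 3-18 points for a 10/90 split in the binge sample at 3.4-4.6% risk. Residual confounding would follow only if coarse strata are the adjuster; the exposure is clearest for cognitive ability.

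The figures assume modification linear in the score, normal or exponential score shapes, an assumed strength of confounding, and logistic or Poisson models standing in for Cox.

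**What to change.** In the data-analysis paragraph under Statistical methods, for RQ 2-3:

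- In the models asking whether distress or ability accounts for the alcohol effect, adjust for the continuous score through a spline, and name cognitive ability explicitly as an adjuster in those models.
- Test interaction with the product of the alcohol term and the continuous score, with a spline check of linearity.
- Keep the strata for presenting hazard ratios and as a pre-specified companion test of interaction.
- Leave the registry diagnosis of mental health problems categorical.

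The cost is a few sentences and a little modelling, with no new data. The downside is lower power for the linear term if modification is a pure threshold; the retained strata test is there for that case.

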## Research questions (RQ)

- (1) To investigate the risk and protective effects on CVD morbidity and mortality associated with various combinations of moderate alcohol consumption and binge drinking. We will here also look at risk in the sub-group of patients with pre-existing CVD.
- (2) To investigate if the effects of moderate alcohol consumption and binge drinking on CVD can be explained by or interact with mental distress (depression and/or anxiety).
- (3) To investigate if the effects of moderate alcohol consumption and binge drinking on CVD can be explained by or interact with cognitive ability (IQ), educational level, or other socioeconomic factors.
- (4) First, to investigate how alcohol consumption in family members are related to CVD risk among index individuals. Secondly, to use alcohol consumption among siblings and offspring as instrumental variable to assess the causal effects of alcohol consumption pattern on CVD.
- (5) Using pairs of siblings, monozygotic and dizygotic twins discordant for CVD to estimating the association between moderate alcohol and binge drinking and CVD within families. These results will adjust for early life and family factors.
- (6) To assess familial aggregation of mental distress, alcohol related mortality and CVD morbidity and mortality.

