### **Samples (sub-populations)**

#### **RQ 1:**

The CONOR and the NTR will be pooled together and the NTR will be used as a cohort for this purpose. This will include n=47,848 from CONOR and n=8028 individuals from NTR (n=55,876 in total) with complete data on both moderate and binge drinking. Mean year of birth is 1947 in CONOR and 1941 in the NTR sample. More deaths occur in the NTR (n=1453 deaths) compared to CONOR (n=1805 deaths). Number of CVD deaths in the CONOR sample with follow-up until 2010 is 547. Based on the proportion of CVD mortality and all-cause mortality and number of fatal and non-fatal cases in the FS-database, total

number of cases, including both CONOR and the NTR is expected to be 3000 IHD and 3500 cases of stroke.

RQs 2 and 3:

This will include the CONOR and twin populations linked to the FS-data on hospital discharges, the Cause of Death Registry, the Conscript Registry (cognitive ability) and Social Security Registry (mental health problems). Two separate sub-populations of CONOR will be studied: all subjects who responded to items on moderate alcohol consumption (n=162,048) and, nested in this sample, those who responded to items on both moderate and binge drinking (n=47,848). In the first group there are 3774 deaths from CVD. There are in total 9735 acute myocardial infarction and 8926 stroke incident cases from the FS-database in CONOR. For the second group, see RQ1.

RQ 4:

This issue will be analyzed in a linkage between CONOR, cardiovascular health surveys in the Norwegian Family Based Life course study and the FS-data on hospital discharges. There are 116,037 individuals in CONOR with information on parents and siblings. Of these, 109,800 individuals have responded on the moderate alcohol consumption question with 9729 CVD deaths in fathers and 31,050 on the binge drinking question with 1854 CVD deaths occurring after the year of CONOR examination.

RQ 5:

CONOR: There are 48,401 siblings in CONOR with the same mother and father. 1025 of these have by 2010 died (281 CVD). We expect approximately 1400 CVD endpoints in the FS-database. For the second group on siblings, see RQ 1.

RQ 6:

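### The stated adjustment set leaves out sex, although the protocol reports more frequent binge drinking in men, so the binge hazard ratio is open to confounding by sex.

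*Protocol*

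**What the plan says.** Under Statistical methods (Data analysis) the protocol says that "the primary modelling strategy is to use Cox proportion hazard regression models". For RQ 1, "the effect of moderate alcohol consumption will be analysed by adjusting for binge drinking and across strata of binge drinking", with an interaction term as the formal test. RQ 2 and 3 follow the same approach, with strata of cognitive ability and mental health.

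One sentence then names the covariates: "Age, smoking status and number of cigarettes per day in smokers, physical activity, self-reported disease (CVD, diabetes, antihypertensive medication) and psychosocial distress at baseline". These "will be adjusted for as potential confounders". The sentence has no wording that marks the list as a set of examples.

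Under Main variables, Binge drinking, the CONOR sample is described by sex ("In all 47,848 participants (26,151 men and 21,697 women") and the protocol adds that "the frequency was a higher in men than in women".

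Under Samples, RQ 1, "The CONOR and the NTR will be pooled together and the NTR will be used as a cohort for this purpose".

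**The concern.** Sex is linked to the exposure by the protocol's own account. If it is also linked to CVD, it confounds the binge effect, and a model without it credits part of the male excess risk to binge drinking. RQ 1 depends on separating the effects of moderate and binge drinking, so this reaches the main question. A large sample does not help: it narrows the interval around a biased estimate.

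The pooled RQ 1 model raises a lesser question. CONOR and the twin registry (NTR) differ in baseline period, in mortality and in how alcohol was asked about, and no cohort term or stratum is named. NTR also contributes complete twin pairs, whose outcomes are not independent.

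**Working it through.** **Is sex handled anywhere else?** The stated covariates are age, smoking, physical activity, self-reported disease and distress. The stated strata are binge drinking, cognitive ability and mental health. Sex is in neither group. Two designs limit sex differences by construction. The conscript test covers men, so cognitive-ability analyses are in effect confined to men. The twin pairs from the 1980 questionnaire are described as like-sexed. Neither covers the main RQ 1 model. CONOR siblings in RQ 5 are defined only by having the same mother and father, so brother-sister pairs are included.

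**Counts from the protocol.**
- 26,151 + 21,697 = 47,848, as stated. Male share = 26,151 / 47,848 = 0.547.
- 47,848 + 8,028 = 55,876, as stated for the pooled sample.
- 46.3% report no binge episode, so 53.7% report at least one.

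**Assumptions, because the documents give no figure.** The gap *d* between men and women in any binge drinking is 5 to 36 points. The male:female CVD ratio *R*, given the other covariates, is 1.5 to 3. Reducing binge frequency to any versus none is a further simplification.

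**Formula for an omitted binary confounder** (risk-ratio form, taken as an approximation for the hazard ratio):

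factor = [1 + P(male | binge)(R − 1)] / [1 + P(male | no binge)(R − 1)]

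**Worked case, *d* = 20 points, *R* = 2.**
- Binge in women = 0.537 − 0.20 × 0.547 = 0.428; in men, 0.628.
- P(male | binge) = 0.628 × 0.547 / 0.537 = 0.639.
- P(male | no binge) = 0.372 × 0.547 / 0.463 = 0.439.
- Factor = 1.639 / 1.439 = 1.14.

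| Gap *d* (points) | *R* = 1.5 | *R* = 2 | *R* = 3 |
|---|---|---|---|
| 5 | 1.02 | 1.03 | 1.05 |
| 10 | 1.04 | 1.07 | 1.10 |
| 20 | 1.08 | 1.14 | 1.21 |
| 30 | 1.13 | 1.22 | 1.34 |
| 36 | 1.15 | 1.26 | 1.42 |

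Every cell exceeds 1, so the direction is upward whenever *R* > 1. For scale, a true binge relative risk of 1.45 (the main-effect value in the power section) would appear as 1.45 × 1.02 = 1.48 at one end and 1.45 × 1.42 = 2.06 at the other.

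**Cohort.** Deaths are 1,453 / 8,028 = 18.1% in NTR and 1,805 / 47,848 = 3.8% in CONOR. The CONOR surveys date from 1994-2003 and the NTR binge questionnaire from 1990. CONOR asks for a count of occasions of at least five glasses of liquor. NTR offers categories and sets other thresholds by type of drink. Binge prevalence in NTR is not given. If it lies between 20 points below and 10 points above CONOR's 53.7%, and the age-adjusted cohort rate ratio is 1.2 to 2.4 (both assumed), the same formula gives 0.89 to 1.06. With equal prevalence it gives 1.00.

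**Twin pairs.** The 1990 questionnaire has 2,138 complete pairs, or 4,276 people. If all are in the RQ 1 sample, they are 4,276 / 8,028 = 53% of NTR and 4,276 / 55,876 = 8% of the pooled sample.

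**The case against.** The strongest reply is that this is a grant-style proposal covering six questions, in which one sentence on confounders need not be exhaustive. The protocol does not say that only these variables will be used, or that every model uses the same set. Sex may well have been left out by oversight, and an analysis plan could add it. This stands as a caution: the list should not be called closed. It does not remove the point, because the protocol did not defer its covariates. It named them, and sex is missing.

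The objection on size also stands. Neither binge prevalence nor CVD risk is given by sex, a small gap makes the bias slight, and smoking and the other listed covariates may absorb part of it. The calculation concerns the binge main effect. It gives no figure for the moderate-drinking effect or the interaction, and 1.45 is an input to the power calculation, not a target effect.

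Two stronger readings are tempting and fail:
- A reader might infer from 18.1% against 3.8% that cohort differences are being attributed to alcohol. These are crude all-cause deaths. NTR has the earlier mean birth year (1941 against 1947) and an earlier baseline, age is in the model, and Cox regression handles follow-up time. Without binge prevalence by cohort, confounding by cohort is not shown.
- A reader might infer that RQ 2, which asks whether the alcohol effects "can be explained by or interact with mental distress (depression and/or anxiety"), cannot be answered because distress is on the list. The protocol gives RQ 2 and 3 their own adjust-and-stratify strategy, and nothing rules out a model without distress.

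**Conclusion.** The omission of sex is a real fault in the stated text. Followed as written, the adjustment set gives a binge hazard ratio biased upward, provided that men have the higher CVD risk given the other covariates. That condition is assumed, because the documents report no CVD rate by sex. The size is unknown: about 1.02 to 1.4 under the assumed ranges, before any absorption by the listed covariates.

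The cohort term is supported only as a safeguard, with the direction of any bias open. Clustering on twin pair follows from the design and concerns standard errors, not the estimate. Whether distress (RQ 2) and education (RQ 3) explain the effect is a matter of clarifying the model sequence, not an error.

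**What to change.** Add sex to the adjustment set in the Data analysis paragraph, or state that the baseline hazard of the Cox models is stratified by sex.

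In the pooled RQ 1 model, also stratify the baseline hazard by cohort (CONOR, NTR) and use standard errors clustered on twin pair.

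As a clarification only, say that RQ 2 will compare models with and without distress, and RQ 3 models with and without education. Treat the two variables alike, since the protocol asks the same kind of question of each.

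The cost is protocol wording and model code, with a few more terms or strata. Sex and cohort are already in the data, and no sample size, power or alpha figure changes.

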The project will use novel approaches by taking advantage of family based designs to understand how both alcohol consumption pattern and CVD risk is patterned across generations and to study how much of the association between alcohol use and CVD may be accounted for by early life socioeconomic environment and shared family factors. Two approaches will be used: *i*) instrumental variable analysis using alcohol consumption among family members as instrument for own consumption and risk of CVD (RQ 3), and *ii*) fixed effect cotwin/sibling analysis (RQ 4) to adjust for shared early life socioeconomic environment and other family factors.

Alcohol consumption and cardiovascular risk may share common causes and artificially inflate estimates of risk. Alcoholism is heritable (heritability 0.52-0.64) and 50 % of the genes involved are shared by full siblings or parents. Several studies suggest that parental alcohol use increases the risk of early alcohol debut and subsequent drinking patterns among children also indicating cultural heritability. Our multigenerational approach investigate if alcohol use and CVD risk is jointly related across generations.

The association between moderate alcohol consumption and CVD mortality resembles the association between body mass index (BMI) and CVD mortality as both have a J-shaped

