relationship in which the lowest group (underweight and abstainers) has increased risk compared to those in the moderate categories. Reverse causality by unmeasured health problems may explain this pattern in these groups. In a Swedish intergenerational study, offspring BMI was used as an instrumental variable for own BMI as BMI in the offspring is less likely to be affected by health problems. The authors found less adverse consequences of lower BMI compared to conventional observational studies. Alcohol consumption in family members can be used similarly as instrument for own consumption to avoid the problem of sick quitters potentially producing non-causal increased risk compared to moderate drinkers (RQ 3). In both cases offspring alcohol and BMI are recorded earlier in life whereas CVD in parents is recorded at a higher age. More generally, using family proxies for exposure might be valuable not only to reduce reversed causality, but also because their alcohol intake will be less strongly associated with the individuals' other risk factors that predisposes him/her for CVD, i.e smoking and diet, and give less biased estimates of effect than own alcohol exposure.

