### **Data sources**

The Cohort of Norway (CONOR) Data from 10 epidemiological studies (n=181,891) from 1994-2003 have been merged into a national database. All the surveys included self-reported health and selected diseases, various risk factors, socio-demographic factors, use of medications and physiological measures such as blood pressure, cholesterol, triglycerides, waist and hip circumference, height and weight.

The Norwegian Twin Registry (NTR) Panel II were born 1915-1960. Questionnaires on alcohol consumption were sent out in 1980 and 1990 and 14 500 responded to one of these. These questionnaires included detailed reports on health and risk factors.

Norwegian Family Based Life course Study Data from all 7,400 000 Norwegian citizens alive between 1960 to 2010 has been linked to family data and several health surveys and registers. Family linkage is available for more than 90 % of those born after 1940. This is linked to several other cardiovascular health surveys in addition to CONOR (in total 730,000) and the Conscript Registry.

Hospital discharges on cardiovascular diseases in Norway (FS-data): Data on all cardiovascular hospitalizations in Norway between 1994 and 2009 has been obtained through patient administrative systems at Norwegian hospitals. This includes coronary heart disease (both myocardial infarction and unstable angina), stroke and atrial fibrillation.

Social security registry (FD-trygd): Data on disability pension, sickness and social security benefits on all Norwegian citizens from 1992 onwards. Diagnosis will be ICD-10: F01-F99 (Mental, behavioral and neurodevelopmental disorders)

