Cardiovascular risk factors: Current smoking, pack years of smoking, Body weight, Height, Waist circumference and Hip circumference, heart rate, systolic and diastolic blood pressures, non-fasting serum total, HDL cholesterol and triglycerides and physical activity.

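### The stated adjustment set has no measure of body size, though height and weight are collected in CONOR; the alcohol hazard ratios should be reported with and without baseline BMI

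*Protocol*

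**What the plan says.** The Data analysis paragraph under Statistical methods holds the only adjustment list in the protocol. It begins "Age, smoking status and number of cigarettes per day in smokers, physical activity, self-reported disease" and ends by stating that "physical activity, self-reported disease (CVD, diabetes, antihypertensive medication) and psychosocial distress at baseline will be adjusted for as potential confounders". No body-size measure appears in it.

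The data exist, at least in CONOR. Data sources says that all the CONOR surveys included "physiological measures such as blood pressure, cholesterol, triglycerides, waist and hip circumference, height and weight". The Cardiovascular risk factors paragraph under Main variables lists "Current smoking, pack years of smoking, Body weight, Height, Waist circumference and Hip circumference", but no section gives weight, height, waist or hip a role in a model.

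BMI is mentioned in one other place. Approaches, hypothesis and choice of method says that the alcohol curve for CVD mortality "resembles the association between body mass index (BMI) and CVD mortality", and uses the parallel to introduce reverse causality and the family-member instrument. The same section argues that relatives' intake should be less strongly tied to a person's "other risk factors that predisposes him/her for CVD, i.e smoking and diet" than that person's own intake is.

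**The concern.** The study asks whether the apparent protection from moderate drinking is real or reflects who the abstainers are. Background and status of knowledge describes abstainers as a less healthy and poorer group. Approaches, hypothesis and choice of method promises to examine a wider range of underlying factors than earlier work did. A measured CVD risk factor with no stated role in the models sits badly with that aim.

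The list is also uneven. If BMI was left out because alcohol may act through weight, the same reasoning could apply to diabetes and antihypertensive medication, which are adjusted for and may themselves follow from body size. Smoking and diet are named as risk factors tied to a person's own drinking. Smoking is adjusted for; neither diet nor body size, a plausible measured correlate of diet, is.

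What is at stake is the interpretation of the RQ 1 hazard ratios for moderate and for binge drinking. A large cohort does not help, because systematic error does not shrink with sample size.

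**Working it through.** The protocol states no figure that depends on this choice, so there is nothing to reproduce. The text comparison above settles the omission. The arithmetic below only illustrates how large the consequence could be.

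**Inputs from the protocol**
- Assumed relative risks: 0.75 for average consumption and 1.45 for binge drinking (Sample size and power).
- About 3,000 expected IHD cases in CONOR and NTR together (Samples, RQ 1).

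**Inputs that are assumptions**
- BMI gap *d* between drinking groups: 0.5 to 1.5 kg/m2.
- CVD hazard ratio *h* per kg/m2: 1.03 to 1.06, taken as log-linear, which simplifies the J-shape.

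**Step 1: shift.** If abstainers are heavier by *d*, the hazard ratio for moderate drinkers against abstainers is multiplied by h^(-d).
- Low end: 1.03^(-0.5) = 0.985, a shift of about 1.5%.
- High end: 1.06^(-1.5) = 0.916, a shift of about 8%.

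An unadjusted 0.75 would become 0.75/0.985 = 0.76 to 0.75/0.916 = 0.82 after adjustment. If abstainers are lighter, the shift reverses: 0.75 × 0.985 = 0.74 to 0.75 × 0.916 = 0.69.

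**Step 2: share of the assumed effect.** |ln 0.75| = 0.288.
- Low end: 0.5 × ln 1.03 = 0.0148, and 0.0148/0.288 = 5%.
- High end: 1.5 × ln 1.06 = 0.0874, and 0.0874/0.288 = 30%.

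**Step 3: against sampling error.** The standard error of the log hazard ratio is roughly √(1/d1 + 1/d2), where d1 and d2 are the cases in the two groups.
- Cases split evenly: √(1/1500 + 1/1500) = 0.0365, so the shift is 0.4 to 2.4 standard errors.
- 10% of cases in abstainers: √(1/300 + 1/2700) = 0.061, so the shift is 0.24 to 1.4 standard errors.

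The protocol gives no split of cases. The even split yields the smallest standard error and so the most severe comparison.

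**Step 4: could BMI create the whole effect?** The gap needed is |ln RR| / ln h.
- For 0.75: 0.288/ln 1.06 = 4.9 to 0.288/ln 1.03 = 9.7 kg/m2.
- For 1.45: 0.372/ln 1.06 = 6.4 to 0.372/ln 1.03 = 12.6 kg/m2.

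Both are far above the assumed gap. With wider assumptions (*h* 1.02 to 1.08, *d* 0.5 to 2) the factor runs from 1.01 to 1.17. The gap needed to produce 0.75 is then 3.7 to 14.5 kg/m2, still beyond the widest gap assumed.

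**The case against.** **BMI may be a mediator.** Alcohol may change weight, and leaving BMI out is then right for a total effect. This stands as a reason not to report only a BMI-adjusted estimate. It does not explain the list as written, which adjusts for other possible mediators and gives no reason for treating BMI differently.

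**The J-shape text is not evidence of confounding.** A reader might infer from it that the protocol itself treats BMI as a confounder of alcohol. It does not. BMI appears there as a parallel exposure, open to the same artefact from ill health. Two exposures with similar curves do not for that reason confound each other. The passage supports BMI as a CVD risk factor and no more.

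**No weight difference is documented.** A reader might also infer that abstainers and binge drinkers are heavier, so that moderate drinking looks too protective and bingeing too harmful. The protocol reports no weight by drinking group. Poorer health among abstainers could equally mean lower weight. This objection stands in full: presence, size and direction of bias are all assumed.

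**Other parts of the plan absorb some of it.** Physical activity, diabetes and antihypertensive medication carry part of any weight effect, and the sibling and twin analysis in RQ 5 removes the part shared within families. This is true, but differences in weight within pairs remain.

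**The list may not be closed.** It also omits sex and education, although RQ 3 is about education, and a separate analysis plan may add covariates. That is possible. The protocol nonetheless names a list, and the point concerns what it names.

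**BMI may not be available throughout.** Height and weight are named for CONOR only; the NTR questionnaires are described in general terms. NTR supplies 8,028 of the 55,876 people in RQ 1 (14%) and the twins in RQ 5. The fix has to allow for this.

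**Conclusion.** The point holds in a limited form. The stated adjustment set omits body size although the data are collected in CONOR and listed as risk factors, and a mediator rationale is neither given nor applied evenly. Part of any BMI difference between drinking groups may therefore remain in the alcohol hazard ratios.

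Under the illustrative assumptions the shift is about 1.5% to 8%, or 5% to 30% of the assumed log effect of 0.75, in a direction that the protocol does not settle. The calculation is log-linear, so it cannot show that the BMI curve reproduces the alcohol J-shape. Nor does it support a claim that BMI explains the protective effect: within the assumed range it could not. The case for changing the plan is that the sensitivity to body size is cheap to show and bears on the study's central question.

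**What to change.** In the Data analysis paragraph, add a model with baseline BMI, as a spline or in categories because the relation with CVD is J-shaped. Apply it to the Cox analyses of RQ 1-3 and RQ 5 in CONOR, and in NTR where height and weight are available. Report it beside the same model without BMI, fitted to the same people so that missing BMI does not drive the difference. State whether BMI is regarded as a confounder, a mediator or possibly both.

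The cost is one derived covariate, one extra column in the tables and a check of what NTR holds. The downside is that, if alcohol changes weight, the BMI-adjusted estimate removes that mediated part of the effect; showing the two models together makes this visible.
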